### In silico analysis

2.9

Each variant of interest will be annotated and interpreted using Alamut Visual (Interactive BioSoftware), which includes splice site analysis tools (MaxEntScan) and protein function prediction tools (SIFT, Polyphen 2.0, REVEL). The variants presenting gene and protein expression in the uveal tissue will be selected, using the protein atlas database (proteinatlas.org). The function of each gene of interest will be interpreted using Genecards (genecards.org), Uniprot (uniprot.org) and Pubmed (https://pubmed.ncbi.nlm.nih.gov/). Proposed splice site variants will also be analyzed using SPIP and spliceAI software. Differential gene expression between tumor and healthy uveal samples will be explored using GEPIA and Expression Atlas databases.

In addition, an enrichment study will be carried out to determine whether the variants identified by the previously applied filters can be linked to the same molecular pathway. Molecular pathways are already defined by online databases (PANTHER, KEGG, *etc.*). The enrichment and associated statistical calculations are carried out on the basis of a list of genes entered into an on-line computer tool (for example https://www.webgestalt.org/, https://biit.cs.ut.ee/gprofiler/gost).

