#### Primary objective and outcome measure

2.3.1

The main objective is to identify new candidate genes for hereditary cancer predisposition among patients with uveal melanoma. The variants of interest will be selected from the data using the following filters: variants with a frequency <1% (GnomAD), if at least 2 affect the same gene; truncating or missense from a list of cancer genes; and a combined annotation-dependent depletion (CADD) score > 20 (COSMIC Tier1 and Tier2). The variants will then be interpreted using various databases and prediction tools.

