### Biological filters

2.8

For BAP1, MBD4 and all candidate gene of uveal melanoma, all variants whose frequency in the general population is < 1% will be analyzed. Variants will be classified according to the American College of Medical Genetics (ACMG) recommendations. In addition, if a BAP1 or MBD4 variant is identified in patients who have never had a genetic analysis, the result will be confirmed on the saliva sample and a consultation will be organized to report the results.

For all the others genes, the variants of interest will be selected from the data using the following filters: variants with a frequency <1% (GnomAD), if at least 2 affect the same gene; truncating; splice variant with a SPIP and SpliceAI predicted effect or missense with a combined annotation-dependent depletion (CADD) score > 20 from a list of cancer genes (COSMIC Tier1 and Tier2).

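### The enrichment study takes a gene list already filtered for cancer genes; unless the reference set matches the filters, cancer pathways will tend to look enriched because of the filter

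*Protocol article*

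**What the plan says.** The protocol article describes a sequence of selections followed by a pathway test.

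- **Recurrence and rarity** (section 2.8): "variants with a frequency <1% (GnomAD), if at least 2 affect the same gene".
- **Cancer-gene list, primary outcome** (section 2.3.1): "truncating or missense from a list of cancer genes". Here both variant types are tied to the list.
- **Cancer-gene list, biological filters** (section 2.8): truncating variants, splice variants with a predicted effect, and "missense with a combined annotation-dependent depletion (CADD) score > 20 from a list of cancer genes (COSMIC Tier1 and Tier2"). The list may govern all three types or only the last.
- **Tissue expression** (section 2.9): "The variants presenting gene and protein expression in the uveal tissue will be selected".
- **Enrichment question** (section 2.9): "whether the variants identified by the previously applied filters can be linked to the same molecular pathway".
- **Enrichment input** (section 2.9): "The enrichment and associated statistical calculations are carried out on the basis of a list of genes entered into an on-line computer tool". On the pathways: "Molecular pathways are already defined by online databases". Two web tools are given as examples.

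The article names no reference set for the test, whether all genes or a restricted set. It gives no significance level or multiplicity rule either. Sections 2.5 and 2.9 both introduce enrichment as an additional analysis; it is not part of the primary or secondary outcome.

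**The concern.** An over-representation p-value has meaning only relative to a reference set. It asks whether the listed genes fall in a pathway more often than genes drawn at random from that set. If the list could only contain curated cancer genes, and the reference set is genes in general, the comparison is between cancer genes and all genes. Pathways rich in cancer genes then come out as enriched because of the selection, whatever the patients carry.

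The study has about 50 patients and no control group, and enrichment is the only step for which section 2.9 mentions statistical calculations. Its p-values could therefore be read as the study's inferential evidence. A pathway reported as enriched in UM might only restate the filter.

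**Working it through.** **The plan's own figure.** There is none to reproduce: the article gives no list size, background, alpha or number of pathways for this test.

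**Assumed inputs (none from the article).** N = 20,000 genes in a general background; C = 700 genes on the cancer list; n = 10, 20 or 40 genes entered into the tool; Bonferroni over 300 pathways, so the threshold is 0.05/300 = 0.000167. Three null pathways of K genes, k of them on the cancer list:

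- A (strong overlap): K = 300, k = 100
- B (strong overlap, smaller pathway): K = 150, k = 60
- C (weak overlap): K = 100, k = 10

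**Method.** The n genes are drawn at random from the cancer list, so none is related to UM.

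1. Find the smallest x with P(X ≥ x) < threshold for X ~ Hypergeometric(N, K, n). This is what the tool would call significant against a general background.
2. Compute P(Y ≥ x) for Y ~ Hypergeometric(C, k, n). This is how often the filtered list gets there by chance.

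**Worked case: A, n = 40.** Expected hits against the general background: 40 × 300/20,000 = 0.6. Expected from the filtered list: 40 × 100/700 = 5.7. Against the general background P(X ≥ 2) = 0.121 and P(X ≥ 3) = 0.022, so 3 hits suffice at 0.05. P(X ≥ 5) = 0.00031 and P(X ≥ 6) = 0.00003, so 6 hits pass Bonferroni. For the filtered list P(Y ≥ 3) = 0.944 and P(Y ≥ 6) = 0.520.

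**General background, every listed gene from the cancer list** (rate at 0.05 / after Bonferroni):

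| Pathway | n = 10 | n = 20 | n = 40 |
|---|---|---|---|
| A | 43% / 4.1% | 81% / 14% | 94% / 52% |
| B | 21% / 4.7% | 52% / 8.3% | 88% / 25% |
| C | 13% / 0.02% | 3.0% / 0.21% | 11% / 0.15% |

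Row C does not rise steadily with n because the hit count is discrete: with 10 genes one hit suffices at 0.05, with 20 two are needed.

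**Missense-only reading of section 2.8.** Some listed genes now come from outside the cancer list. Let m such genes be drawn at random from the other 19,300. The hit count is Y + Z, with Z ~ Hypergeometric(19,300, K − k, m), and the critical value comes from Hypergeometric(20,000, K, n + m).

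| Pathway | 40 cancer + 40 other | 40 + 200 | 20 + 100 | 20 + 200 |
|---|---|---|---|---|
| A | 88% / 26% | 53% / 4.1% | 35% / 1.2% | 22% / 0.3% |
| B | 72% / 14% | 44% / 2.6% | 17% / 0.5% | 12% / 0.1% |
| C | 3.7% / 0.06% | 6.3% / 0.01% | 3.9% / 0.01% | 3.4% / 0.02% |

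For A and B the effect is diluted but does not vanish. For C it stays near or below the nominal level.

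**Filtered list as reference set.** The critical value now comes from Hypergeometric(C, k, n), the distribution that generated the list. Over A, B and C at n = 10, 20 and 40 the rate is at most 4.7% at 0.05 and 0.014% after Bonferroni.

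**The case against.** The strongest objection is that the article states no reference set. A reader might infer from the bare mention of a gene list that the plan tests against the whole genome and that its pathway p-values are therefore invalid. The text does not say so. A journal article condenses the full protocol, the tools are named only as examples, and a restricted reference set may be specified elsewhere. If it is, the problem disappears. This part of the objection stands, and the conclusion must remain conditional. What remains is more than a missing setting: the article itself states both the filter and the test applied to what survives it, and a person following section 2.9 as written has only the filtered list to enter.

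Second, a reader might take every input gene to be on the COSMIC list. Section 2.3.1 supports that; the more detailed section 2.8 leaves it open. It is also unclear whether the filters preceding enrichment include the uveal-expression selection. Both points stand and are reasons to reconcile the text.

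Third, the size depends on unstated quantities. With short lists or weak overlap the excess is small or absent, so it would be wrong to say that false enrichment is guaranteed.

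Fourth, enrichment is an add-on. The primary outcome selects variants by filters and interpretation, and no pathway p-value enters that selection. This limits the consequence.

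A related worry is that requiring at least two variants per gene favours long genes and distorts pathway tests further. That is plausible but has not been quantified here, and the conclusion does not rest on it.

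**Conclusion.** The concern holds in conditional form. If the filtered gene list is tested against genes in general, pathways rich in cancer genes will tend to appear enriched without any relation to UM. Under the assumed sizes, with all listed genes from the cancer list, the false-positive rate for a single null cancer pathway runs from about 3% to 13% at 0.05 (at most 0.2% after Bonferroni) with weak overlap, up to 94% (52%) with strong overlap and 40 listed genes. A multiplicity correction alone does not cure the strong-overlap case. Under the missense-only reading the strong-overlap rates are lower.

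The documents do not establish that a general background will be used, so they do not support calling the planned p-values invalid. They do establish that the input is pre-selected and that sections 2.3.1 and 2.8 leave the extent of that selection unclear. Severity is moderate: the affected result is supplementary, but the study would report it.

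**What to change.** 1. Reconcile sections 2.3.1 and 2.8 on which variant types the cancer-gene list restricts: truncating, splice, missense, or all three.
2. State in section 2.9 which filters precede enrichment, including whether the uveal-expression selection does, and whether genes handled under the separate rule for BAP1, MBD4 and UM candidates enter the list.
3. Set the tool's custom reference set to the genes that could have passed those filters: COSMIC Tier 1 and 2 where that restriction applies, adequately captured by the exome kit, and expressed in uveal tissue if that filter comes first. If the restriction covers missense variants only, truncating and splice variants can bring in genes from outside the list. The two routes then need either separate tests, each with its own reference set, or a reference that reflects both.
4. Report multiplicity-corrected p-values against that reference set only.

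Optional sensitivity check: a null matched on gene length, or a repeat of the test on genes selected through rare synonymous variants.

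The cost is a few sentences and one tool setting, with no new patients or data, provided it is fixed before the enrichment is run. Separate tests by variant route would add a little work. The downside is fewer significant pathways.

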### Sample size

2.10

Since uveal melanoma is a very rare condition and given the study design, no minimum number of patients to include has been defined. Recruitment of approximately 50 patients is a reasonable estimate of the recruitment capacity.

### Data-management

2.11

All clinical and genetic data will be collected from the patients’ medical records or obtained during consultations with the oncology and genetics teams. The data collected will be limited to what is necessary to meet the specific objectives of the study, including:

Personal history of cancerFamily history of cancers, including a genealogical treeAnatomical pathology reports related to the patients’ tumoral pathologyReports of constitutional and tumor genetic analyses performed on the patients, particularly those related to the occurrence of uveal melanomaReports on genetic analyses related to hereditary cancer risks, if applicableWhole exome sequencing data in VCF format

The data capture for the study will be performed by oncologists-geneticists from the Centre Jean PERRIN Molecular Oncology and Genetics Laboratory. The data will be recorded in an Excel file specific to the study. Individuals who will have access to the data include investigators, project managers, and bioinformatics technicians. These are authorized professionals bound by professional confidentiality, and all data will be made anonymous to ensure confidentiality.

### Trial status

2.12

Patient recruitment for the IGCMU trial is currently on-going and has been so since October 2024.

## Discussion

3

This study aims to explore the hereditary aspects of UM by identifying new candidate genes involved in cancer predisposition. While the roles of BAP1 and MBD4 are already known in family clusters, around 78% of UMs are not linked to them (10). This highlights the need to know what other genes could have an impact on the occurrence of this disease. In order to better understand the mechanisms behind UM and improve patient outcomes, it is essential to continue research in this area. Many research teams are or have been working on this topic. In France, we can cite the Curie Institute and the Melanoma Patient Network Europe, which focus on understanding why some European individuals are at a significantly higher risk and why some patients develop aggressive forms of the disease with a high likelihood of metastasis. This project has obtained American funding under the “Rare Melanomas Focused Program Award” call for proposals with the aim of developing three themes: 1- identifying UM predisposition factors, 2- establishing and identifying isogenic cell lines from the original uveal melanocyte, and 3- identifying recurrent, immunogenic neoantigens specific to UM (15).

One study (NCT05179174) is currently recruiting UM patients in order to identify genetic and epigenetic biomarkers in UM using miRNA analysis, while also focusing on the GNA11 and GNAQ genes. These genes are located on chromosomes 9q21.2 and 19p13.3 and encode for proteins vital for signaling pathways in uveal melanoma (UM). Mutations in these genes have already been studied, and have been identified in approximately 80-90% of UM cases (3, 16). However, they have not been associated with patient outcomes or disease-free survival (17, 18).

One of the limits of our study is the small sample size. We have defined our recruitment capacity according to the number of cases identified in the French national association of patients with eye cancers (A.N.P.A.C.O.), which supports this research. In order to expand the cohort and thank to the *Plan France Médecine Génomique 2025*, we plan to request access to the national sequencing platform data, so that we can add data from other UM patients. Indeed, on a national scale in France, all cases of uveal melanoma occurring before the age of 40 are addressed to, sequenced and stored on this platform.

The possible involvement of genes like BRCA1, BRCA2, CHEK2, and POT1, which are known to play a role in other hereditary cancers, could lead to new knowledge of UM, especially in family cases (12). By conducting exome sequencing and focusing on genes associated with various hereditary cancer syndromes, this research could expand the current understanding of the genetics of UM because of similar biological mechanisms and signaling pathways that could affect its progression. For example, a recent study found that certain mutations in genes involved in the PI3K/AKT/mTOR pathway could have a prognostic value in UM. CHEK2 and PDK1, for instance, have been shown to be associated with the development of metastases, as well as DHX9. This retrospective analysis involved 69 UM cases with a median age of 59 years, and 39% presented metastatic disease at inclusion (19). Given the small size of this cohort, a larger, prospective study could be valuable to validate these findings.

Previous studies have also explored the involvement of BRCA1 (12, 20), BRCA2 (21, 22) and CHEK2 (12). The study examining the relationship between BRCA1 and UM was retrospective. Researchers also analyzed a substantial cohort of BRCA mutation carriers and explored whether any of the 469 cases developed UM. They identified two cases of UM, a frequency higher than the typical incidence in the general population, which is about five to six cases per million inhabitants (20). These findings suggest that pursuing research in this direction could be worthwhile.

One of the studies investigating the involvement of BRCA2 was prospective, conducted in Israel, and included 30% of UM cases in the country in the 1990s. In brief, 149 patients were included, but only 4 out of the 143 assessable patients were found to carry BRCA2 mutations. This limited number of mutations reduced the study’s ability to establish a strong association between this gene and UM (21). The other study exploring the involvement of BRCA2 in UM was also prospective and conducted in the 1990s. It reached a similar conclusion; however, the screening of patients could have been biased, as genomic analyses were preferentially performed on UM cases with a family history of breast or ovarian cancer — cancers that are known to be associated with BRCA mutations (22).

Other genomic analyses found only sporadic associations with UM (2, 21, 22). Some of these studies are 20 years old and current analysis techniques could provide new insights. This is why we have initiated the IGCMU study, in an attempt to find answers to these questions and expand research by including other targets such as PALB2, POT1, MSH6, MLH1, SMARCE1, TP53AIP1, MLH2 and PMS2.

The single-center design of our study enables a close coordination between oncologists, geneticists, bioinformaticians, and clinical staff, ensuring the quality in the process of genetic analysis. This approach is important given the complexity of analyzing genetic data for such a rare condition.

Finally, the identification of new candidate genes could not only improve our understanding of the genetic origins of UM, but also lead to better clinical management for patients and their families.

In conclusion, this study aims to fill a gap in the current knowledge on hereditary predisposition to uveal melanoma. By identifying new candidate genes associated with the disease, this research has the potential to enhance patient care and ultimately improve outcomes for patients with uveal melanoma.
